#### Logbooks

Teachers will be asked to keep track of a logbook during the two sessions. This logbook will consist of a simple checklist in which they can tick the boxes of the components they delivered during the session. Moreover, they will be asked to indicate the time spent on the components and rate their satisfaction with the lesson. Finally, there will be room for additional comments in case they encountered difficulties during the implementation of the lessons.

#### Interviews

All participating teachers will be invited to elaborate on the facilitators and barriers of implementation of the lessons during a semi-structured interview. Data from the logbooks will be used as an input for the interview guide, as well as the diffusion of innovations theory [27]. The topics that will be addressed include teachers’ experiences (e.g. ’How did you experience working with the program?’ or ’How did you like working with the manual?’), dissemination (e.g. ’Would you be interested in using the program again in the future?’) and innovation characteristics (e.g. ’To what extent does the program fit in your schools’ curriculum?’ or ’How complex was it for you to work with the program’?). The interviews are expected to last between 15 and 30 min, will be audio-recorded and will be transcribed verbatim.

#### Google Analytics

The usage of the website will be monitored by Google Analytics. This quantitative measure gives us the opportunity to assess participants’ behaviour on the website objectively. The potential of using this method in the process evaluation of Internet-delivered interventions has been demonstrated before [28]. The data will give us information on when the website is visited and by whom, how participants then behave on the website, whether they complete all elements and, if not, when they quit. This also gives us the opportunity to check whether matched classes in different arms received the program in the same period of time. As emphasized in the previous Internet-delivered interventions study [28], it is important to combine objective user data with qualitative measures. Google Analytics cannot provide an explanation for certain user behaviour, which will therefore be assessed using interviews, logbooks and questionnaires. As Google Analytics can only trace users back to their zip code, teachers will be provided with a link to be able to trace the user behaviour back to specific schools and even classes. User behaviour cannot be traced back on the individual level; only data at the aggregate class level are accessible and used for evaluation purposes.

### Statistical analyses

The first aim of this study is to investigate the effectiveness of the educational program on the intention to register a choice (i.e. the primary outcome in the study at hand, measured as yes or no). All data for the effectiveness are gathered from questionnaire E. Secondary outcomes will be the choice students intend to make (yes or no donation), behavioural determinants and finally their actual registration behaviour 6 months after receiving the intervention. The differences in outcomes between the intervention and the control group will be analysed using multilevel regression models, taking into account that students are nested within classes which in turn are nested within schools. Besides intervention group, several demographic characteristics are included in these models (i.e. sex, study discipline, age, religion and educational level), as they are expected to be associated with the outcomes.

As a post-test only design was used, there are no missing data in terms of participants dropping out in between measurements. Therefore, when comparing the experimental and control groups, missing data will not be an issue—we have all data from participants who agreed to participate. The mixed model analysis is then valid under the assumption of missing at random (MAR). However, when correcting for covariates, missing could become an issue, as participants can skip items in the questionnaire. This will be dealt with using multiple imputation (MI).

The second aim is to analyse the implementation of the program. Interviews will be audio-recorded, and a transcript will be written from each interview. The transcripts will be marked with labels using open coding. These codes will be categorized (selective coding), resulting in matrices in which facilitators and barriers of the implementation will be identified. Quantitative data from Google Analytics, the teachers’ logbooks and students’ questionnaires (questionnaire P) will be used for descriptive analyses to provide insight into how the program was used, delivered and received.

All data will be stored on a secured service and will only be accessible by the study team. A data entry check will be performed on the data from the questionnaires; range checks will also be performed. The interviews will be coded independently by two researchers.

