### Study design

This article was written in accordance with the Standard Protocol Items: Recommendations for Interventional Trials (SPIRIT) checklist (Additional file 2). The effects of the program on registration behaviour, registration intention and beliefs regarding organ donation and registration will be evaluated in a CRCT with post-test only (see Figs. 1 and 2). The program will be offered to both the control and experimental groups. Students in the control group will complete the evaluation questionnaire before receiving the program, while the experimental group will do this after receiving the program. Differential attrition can be prevented, as all participating classes will receive the program. A post-test design prevents the risk of testing bias by priming students for the program by filling out the questionnaire beforehand [22]. The absence of a pre-test, however, might also threaten internal validity, since equivalence of the groups cannot be established. The threat of possible differences at baseline will be minimized by using a large number of randomization units and a proper randomization [23].

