**Fig. 2 Fig2:**
[figure not shown]
SPIRIT figure

After agreement to participate, classes will be matched by members of the study team to improve the equivalence of the groups. The classes will be matched on study discipline, and matched classes will be from the same school. From each pair of matched classes, one class will be randomly assigned to the experimental condition, while the other class will then be assigned to the control condition. Teachers will be notified as to whether they have to hand out the questionnaire before or after delivering the program to students.

The implementation of the educational program will be evaluated using both qualitative (i.e. semi-structured interviews) and quantitative (i.e. logbooks, questionnaires, Google Analytics data) methods, both during and post-delivery.

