### Procedure

The educational program will be provided by the teachers in IVE schools during regular classes. They will receive a link via e-mail prior to the start of the study. With this link, both teachers and students can reach the website. Before the first lesson, the control group will complete the effect evaluation questionnaire. All participants will then receive lesson 1, with the video fragments and group discussions. During the next session, they will both receive lesson 2a, the quizzes with tailored feedback, and lesson 2b, the exercise on completing an organ donation registration form. Teachers will have the freedom to provide the lessons whenever it fits their schedule, but we expect that in most cases lesson 2 will be delivered within 1 or 2 weeks after lesson 1. After the whole program is delivered, students in the experimental group will fill in the evaluation questionnaire. Six months after the implementation of the program, participating students (students from both the experimental and control groups) will receive a follow-up questionnaire during class to measure their registration behaviour. New control classes will then be recruited to compare the registration behaviour of students who received the program with that of students who did not. Data for the process evaluation will be gathered partly during the program delivery and partly after. During the program delivery, data will be collected on usage (e.g. by means of Google Analytics), while after the program delivery, reasons for particular usage behaviour will be assessed (e.g. by means of interviews). Moreover, students in the experimental groups will complete a process evaluation questionnaire after the program is delivered.

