#### Questionnaires

All students will participate in the evaluation study by completing a total of two or three questionnaires depending on the condition: one for the process evaluation (questionnaire P; experimental condition only), one for the effect evaluation (questionnaire E) and one follow-up questionnaire (questionnaire F). For the process evaluation, only students in the experimental condition will receive a questionnaire (questionnaire P) in which they are asked to evaluate the program after the second session. This questionnaire will assess the *dose received* and *reasons for fidelity and dose*. *Dose received* will be measured by assessing their appreciation for the program. The appreciation of the program as a whole as well as the three components will be assessed by asking the students how much they learned from each component and how much they enjoyed working with the component. Also, *reasons for fidelity and dose* will be assessed by asking students what parts they liked and what parts could be improved.

The questionnaire for the effect evaluation (questionnaire E) will be completed before (control condition) or after (experimental condition) the program delivery. The primary outcome will be the students’ intention to register (yes/no). Students who answered ‘yes’ to this question will be asked to specify the decision they would like to make (registering as a posthumous organ and tissue donor, a posthumous donor for specific organs and tissues or a non-donor; leaving the decision to the next of kin; or leaving the decision to a specific person), which will be dichotomized into intention to become a donor or not. All students will also be asked about whether they already registered a decision (yes/no) and, if yes, the choice they made (see the above-mentioned options). Only unregistered participants will fill in the intention question. Additionally, questions are included to measure attitude, self-efficacy, knowledge and social outcomes. These behavioural determinants are the main focus of the educational program.

Finally, all participants will receive a follow-up questionnaire (questionnaire F) after a period of approximately 6 months to measure their registration behaviour. As official registration records are private, participants will be asked whether they registered their choice since receiving the program and, if so, what choice they registered.

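### Registration status at questionnaire E is the trial's only randomised comparison of registration with and without the program, but it is not listed as an outcome

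*Protocol article*

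**What the plan says.** All references are to the protocol article.

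- **Aim.** The Aims section includes actual registration behaviour among the effects to be studied. Study design ties it to the randomised post-test-only trial: "The effects of the program on registration behaviour, registration intention and beliefs regarding organ donation and registration will be evaluated in a CRCT".
- **Allocation and timing.** Below Fig. 2: "From each pair of matched classes, one class will be randomly assigned to the experimental condition". Matched classes come from the same school. On questionnaire E, Study design states: "Students in the control group will complete the evaluation questionnaire before receiving the program, while the experimental group will do this after receiving the program".
- **Registration item in questionnaire E.** Questionnaires: "All students will also be asked about whether they already registered a decision (yes/no) and, if yes, the choice they made". Only unregistered students then answer the intention question, which is the primary outcome.
- **Outcomes.** Statistical analyses names intention to register as primary. The secondary outcomes are the intended choice, "behavioural determinants and finally their actual registration behaviour 6 months after receiving the intervention". The same section says that all effectiveness data come from questionnaire E, yet six-month registration is collected with questionnaire F.
- **Six-month comparator.** Study design: "The program will be offered to both the control and experimental groups". Procedure: "New control classes will then be recruited to compare the registration behaviour of students who received the program with that of students who did not". No randomisation of these new classes is described.

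**The concern.** An aim of the randomised trial is matched to an outcome that the randomisation does not serve. At six months neither randomised arm is an unexposed group, and the new control classes are described only as recruited. If the outcome list is followed as written, the trial gives no randomised program-versus-no-program estimate of registration, although Study design promises one and the data for it will exist.

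There is a second reason to look at the item. Registration status decides who answers the primary intention question, and it is recorded after the program in the experimental arm only. A student whom the program prompts to register at once drops out of the primary denominator in that arm. Reporting status by arm would show whether this happens, and how often.

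**Working it through.** **1. Which registration comparison is randomised?**

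| Measurement | Randomised control classes | Randomised experimental classes | No-program group |
|---|---|---|---|
| Questionnaire E | before the program | after the program | the randomised control classes |
| Questionnaire F, about 6 months | after the program | after the program | new classes, no randomisation stated |

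Only the first row compares program with no program between randomised classes. The outcome list contains only the second.

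**2. The plan's own sample-size figures** (Study setting, population and sample size)

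- Unregistered students per class: 16.2 × 0.738 = 11.96, rounded to 12.
- Schools: 12 × 1.15 = 13.8, rounded up to 14.
- Unregistered students: 14 × 10 × 12 = 1680.

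These reproduce. The stated power of 0.839 for the primary outcome can be neither confirmed nor refuted, because the control intention rate and the random-effect variances are not given. This point does not depend on it.

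**3. What a comparison at questionnaire E could detect**

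Inputs from the article: 140 classes (70 per arm), 16.2 students per class, 73.8% unregistered and so 26.2% registered in control classes. Assumption: the ICC for registration status is not given, so I take 0.02 to 0.05. The article uses 0.02 at class level and 0.01 at school level for the primary outcome. Because both arms occur within each school, I inflate for class only. I also assume that every student consents and answers.

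- Students: 140 × 16.2 = 2268, or 1134 per arm.
- Design effect at ICC 0.02: 1 + (16.2 − 1) × 0.02 = 1.304.
- Effective number per arm: 1134 / 1.304 = 870.
- 95% CI half-width: 1.96 × √(2 × 0.262 × 0.738 / 870) = 0.041, or 4.1 points.
- Detectable difference: power solved for 80%, two-sided 5%.

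| Assumed ICC | Design effect | Effective n per arm | Detectable difference | Power, 2 points | Power, 5 points | Power, 8 points |
|---|---|---|---|---|---|---|
| 0.02 | 1.304 | 870 | 6.1 points | 15% | 64% | 95% |
| 0.03 | 1.456 | 779 | 6.5 points | 14% | 59% | 93% |
| 0.05 | 1.760 | 644 | 7.1 points | 12% | 51% | 88% |

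The 15% increase in schools was made because class sizes vary. If that variation uses it up, the design is worth 120 equal-sized classes: 60 × 16.2 = 972 per arm, 972 / 1.304 = 745 effective, and a detectable difference of about 6.6 points at ICC 0.02.

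A 6.1-point rise means that about 6.1 / 73.8 = 8.3% of unregistered students register before completing questionnaire E.

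**4. Illustration of the effect on the primary denominator**

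Assume a control intention rate of 45% (the article gives none), that the students who register early are ones who would otherwise have said yes, and no other effect on intention.

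- Intenders as a share of all students: 73.8% × 0.45 = 33.2%.
- 5 points register before questionnaire E: (33.2 − 5) / (73.8 − 5) = 28.2 / 68.8 = 41.0%.
- 3 points register: 30.2 / 70.8 = 42.7%.

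Measured intention would fall by about 4 or 2.3 points although the program had worked. This shows a mechanism; it is not an estimate of how often it occurs.

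**The case against.** The strongest reply is that this asks for one more analysis. A condensed article may leave the by-arm comparison of a collected item to an analysis plan that is not shown, and nothing excludes it. The Abstract lists registration status among what the questionnaire assesses and says it is assessed again at six months. Registered students are also asked which choice they made, which a mere filter would not need. This stands in part. A reader might infer that the trial discards the item or will never compare it between arms. The text does not support that; it is inconsistent rather than exclusionary. But the article does give an explicit list of secondary outcomes, and that list does not match the aim stated under Study design.

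A reader might also infer that the comparison at questionnaire E is an unconfounded answer to the registration aim. That is too strong:

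- Status is self-reported.
- The experimental arm answers later by design.
- The Discussion expects that control students may hear the content first, and says this would probably lead to underestimation.
- Only experimental students will just have practised completing a registration form. Some might report the exercise as a registration, though the article gives no evidence of this.
- The window is short. Lesson 2 is expected within one or two weeks of lesson 1 in most classes, and questionnaire E follows the program.

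With power of about 15% for a 2-point rise, a null result is quite possible and would say little. All of this limits what the comparison can show. None of it removes the reason to list it.

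Finally, the six-month outcome should not be demoted because of this. It addresses the longer-term behaviour that the protocol targets, and the Discussion already admits that it gives only limited insight.

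**Conclusion.** The point holds as a mismatch between aim and outcome list. Registration behaviour is an aim of the randomised trial, the listed registration outcome has no randomised no-program group, and the one randomised contrast available, status at questionnaire E in all students, is not listed.

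The gain from listing it is real but modest: a randomised estimate of short-term, self-reported registration with a detectable difference of about 6 to 7 points. That rests on an assumed ICC of 0.02 to 0.05, the preparatory study's class size and registered share, and full response. Small immediate rises would probably be missed, and later effects lie outside its reach. It also provides a check on who enters the primary analysis. This is a cheap improvement that the sponsor should make; it does not invalidate the primary comparison or the six-month follow-up.

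**What to change.** 1. In Statistical analyses, add a secondary outcome: registered a choice at questionnaire E (yes/no), all students, compared between randomised arms with the same multilevel model. Describe the registered choice by arm.
2. State its limits: self-report, a window of about one to two weeks, possible contamination of control classes, and that a null result does not exclude later effects.
3. Keep the six-month registration outcome, and label its comparison with the newly recruited classes as non-randomised.
4. Reconcile Study design, Procedure and Statistical analyses on where registration behaviour is evaluated, and correct the statement that all effectiveness data come from questionnaire E, since the six-month outcome comes from questionnaire F.
5. Report the number registered at questionnaire E by arm next to the primary result, so that any shift out of the unregistered group is visible.

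The cost is a few lines of text and one extra model on data already being collected. No new classes, questionnaire items or follow-up are needed.

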Data from a preparatory study in the same target group [20] and the evaluation of a similar study in a slightly different target group [11] were used in simulations to calculate the sample size for the current study. The calculations were performed using a Monte Carlo simulation study with MLPowSim and are therefore not based on design effects, but on the expected percentage of registration in the control and experimental groups as well as the variances of the random effects from the logistic multilevel model and intraclass correlations (ICCs) [24]. The calculations were based on an expected increase in the primary outcome, expected class size, the ICC and the power of the test. The matching was not taken into account, as this will only increase the power. Therefore, the chosen power level (80%) is a safe choice [25]. A relative increase of 20% of the primary outcome was minimally expected based on the results of the study by Reubsaet et al. [11]. In the preparatory study, the average number of students per class was 16.2, of which 73.8% were not registered yet (our target group). The average cluster size is therefore 11.95, or 12 unregistered students per class. In order to be able to detect a difference of 20% with 80% power in a two-sided test with α = 0.05, taking into account an ICC of 0.02 at class level and 0.01 at school level, the required sample size is 12 schools, with an average of 10 classes per school and 12 unregistered students per class, leading to a power level of 0.839. However, as there is a high range of the number of students per class, the number of schools is increased by 15% [26], resulting in a minimum of 14 schools (and thus 140 classes, of which 70 are assigned to the control condition and 70 to the intervention condition, with a total of 1680 unregistered students).

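### Classes are randomised within matched pairs, but the stated model has no pair level, so the treatment standard error can be somewhat too large; a pair random intercept is a cheap remedy

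*Protocol article*

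**What the plan says.** In the protocol article, the Study design section sets out the matching and allocation: "The classes will be matched on study discipline, and matched classes will be from the same school". It continues: "From each pair of matched classes, one class will be randomly assigned to the experimental condition", and the other class of the pair goes to control.

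The Statistical analyses section describes the models for all outcomes as multilevel regressions "taking into account that students are nested within classes which in turn are nested within schools". Besides the intervention group, "several demographic characteristics are included in these models (i.e. sex, study discipline, age, religion and educational level") . Study discipline therefore enters as a main effect and school as a level. Matched pair is not named.

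The section on study setting, population and sample size says of the power calculation: "The matching was not taken into account, as this will only increase the power". It concludes from this that the 80% power level is a safe choice.

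**The concern.** The analysis should reflect the groups within which treatment was randomised. Here that group is the pair, and the listed levels pass from class straight to school.

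The two matching factors are present, but only as main effects. A main effect of discipline assumes the same discipline effect in every school. It does not capture what is particular to one discipline in one school, nor a teacher shared by both classes. The Discussion makes the second source plausible, since it expects one teacher often to have classes from both arms in a school.

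Within a pair, this shared part cancels from the treatment contrast. A model without a pair term leaves it in the class variance and charges it to the standard error. At stake are some precision and interval width that the design has already paid for.

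**Working it through.** **1. Inputs from the sample-size section.** 12 schools × 10 classes × 12 unregistered students; "taking into account an ICC of 0.02 at class level and 0.01 at school level"; two-sided α = 0.05; stated power 0.839; then 14 schools, 140 classes and hence 70 pairs. The effect is described as "A relative increase of 20% of the primary outcome was minimally expected". (The Abstract gives 13 students per class; the 12 of the sample-size section is used here.) The control-arm rate is not given and is assumed below.

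**2. The plan's own figure.** Arms are compared within schools, so the school component cancels. With m = 12 and C classes per arm:

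Var per arm = p(1−p) × [0.02 + (1 − 0.02 − 0.01)/12] / C = p(1−p) × 0.1008 / C.

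With 12 schools, C = 60. Taking p₁ = 1.2 p₀, power is 0.597 at p₀ = 0.30, 0.796 at 0.40, 0.876 at 0.45 and 0.936 at 0.50. It equals 0.839 at p₀ ≈ 0.425: the difference is 0.0850, the SE is √(0.4943 × 0.1008/60) = 0.0288, and 0.0850/0.0288 − 1.96 ≈ 0.99. The figure is therefore attainable from the stated inputs with no term for matching. An absolute 20-point difference would give power of about 1.00 and does not fit.

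**3. Ceiling on the effect of a pair term.** Let f be the share of class variance common to a pair. Pairing removes it, so the class term becomes (1−f) × 0.02. If a model recovered none of this, its SE relative to the paired SE would be:

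- f = 0.25: √(0.1008/0.0958) = 1.03
- f = 0.5: √(0.1008/0.0908) = 1.05
- f = 1: √(0.1008/0.0808) = 1.12

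The documents give no f.

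**4. Simulation with discipline in the model.** 14 schools × 5 pairs × 12 students per class, with assumed rates of 0.40 and 0.48 and 2,500 runs per scenario. Linear models on class means stand in for the planned logistic multilevel model. The model without pairs has school and discipline effects; the comparator is the within-pair analysis. The second column is the part of the pair similarity that discipline main effects explain.

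| f | Explained by discipline | SE, no pair term | SE, paired | Ratio | Type I error, no pair term | Power, no pair term | Power, paired |
|---|---|---|---|---|---|---|---|
| 0 | – | 0.0265 | 0.0265 | 1.00 | 0.051 | 0.840 | 0.840 |
| 0.5 | all | 0.0251 | 0.0251 | 1.00 | 0.045 | 0.891 | 0.886 |
| 0.5 | half | 0.0257 | 0.0252 | 1.02 | 0.050 | 0.868 | 0.872 |
| 0.5 | none | 0.0263 | 0.0251 | 1.05 | 0.040 | 0.871 | 0.886 |
| 1 | all | 0.0237 | 0.0237 | 1.00 | 0.044 | 0.914 | 0.914 |
| 1 | half | 0.0250 | 0.0237 | 1.05 | 0.042 | 0.894 | 0.906 |
| 1 | none | 0.0261 | 0.0237 | 1.10 | 0.034 | 0.890 | 0.923 |

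The Monte Carlo standard error is about 0.004 for the type I error (√(0.05 × 0.95/2500)) and about 0.0065 for power near 0.88. The 0.840 in the first row belongs to 14 schools at a control rate of 0.40; its closeness to 0.839 is coincidence.

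In every row with pair similarity, the model without a pair term has more power than the 0.840 of the first row.

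**5. Cost of a pair term that is not needed.** In the first row the two analyses differ by less than 0.1 point. A second simulation used 12 schools, 60 pairs, assumed rates of 42.7% and 51.2%, 4,000 runs and school adjustment only. With no pair variance it gave 0.836 with pairs and 0.8435 without, a loss of 0.75 points.

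**The case against.** The strongest reply is that both matching factors are already in the model, so most of the pairing may be represented. Where discipline explains the whole pair similarity, the table shows no loss. This stands, and it is why the inflation can only be stated conditionally. What remains is similarity that main effects cannot carry, and its size is unknown.

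A second reply is that a journal article compresses the model, and the full random-effects structure may be in an analysis plan that is not shown. That is fair as a caution. But the article does not leave the levels open: it lists them. If the fuller plan has a pair term, the article's sentence only needs aligning with it.

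A reader might also infer more than the documents support:

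- *That the gain from matching is lost without a pair term.* It is not. Power rose with pair similarity in every scenario; only part of the gain can be lost.
- *That the standard errors are too large.* They can be, depending on an unstated share and on how much discipline explains.
- *That the sample size relies on a gain the analysis does not take.* The 0.839 uses class and school ICCs only, the same levels as the analysis, and gives matching no numerical credit.
- *That the test is invalid.* The error is in the conservative direction.

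**Conclusion.** The stated model does not follow the randomisation at the pair level. The consequence is a possible, modest loss of precision and not an error in the power or a threat to validity.

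For 50% to 100% of class variance common to the pair, the treatment SE is inflated by 0% if discipline explains all of the similarity, about 2–5% if it explains half, and about 5–10% if it explains none. In the last case type I error falls to about 0.034–0.040 and power by about 1.5–3 points. The formula's 12% is an outer bound, because it lets school and discipline absorb nothing.

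These sizes rest on an assumed control rate of 0.40, the plan's ICCs, equal classes of 12, and class-mean models in place of the logistic multilevel model. The class ICC of 0.02 keeps the effect small. This is a near-costless improvement that is worth fixing in advance, which also removes a later choice between paired and unpaired models.

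**What to change.** In the Statistical analyses section, make the nesting student in class in matched pair in school, with a random intercept for pair. For the primary outcome:

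logit P(intends to register) = β₀ + β₁ × arm + covariates + school + pair + class,

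with the last three terms random. Apply it to the primary model and to the secondary models that compare the randomised classes. It does not carry over to the six-month comparison with newly recruited control classes, which are not members of the randomised pairs.

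The cost is one more variance component, estimated over 70 pairs, and under 1 point of power if pairs share nothing. If the pair variance is estimated at zero, the model reduces to the planned one. The number of schools does not change.

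Optionally, qualify the sample-size sentence on matching to say that the full gain requires the pairs to be modelled.
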